### Outcomes

The primary outcome is the percentage variation in baseline EHP30 questionnaire scores between the pre-operative visit and at 1 year after surgery.

To measure QoL, the authors chose the EHP-30 questionnaire, one of the most frequently used scales for quantification of perceived health, specific to endometriosis [11].

The EHP-30 contains 30 items ranging from 0 (best health status) to 100 (worst health status). The core questionnaire items are grouped into 5 main scales: pain (11 items), control and powerlessness (6 items), emotional well-being (6 items), social support (4 items) and self-image (3 items). A modular questionnaire, that may not apply to all women with endometriosis, comprises 23 items grouped into six scales: ‘Work’ (5 items), ‘Relationship with children’ (2 items), ‘Sexual intercourse’ (5 items), ‘Medical profession’ (4 items), ‘Treatment’ (3 items), and ‘Infertility’ (4 items) [7].

Secondary outcomes are listed below:

1/- a/The following validated questionnaire scores: EHP-30, GIQLI (digestive function), FSFI (sexual function), ICIQ-FLUTS (urinary tract symptoms) and PCS (pain catastrophizing) evaluated at the pre-operative visit, and at 6 and 12 months.- b/VAS of pelvic pain reported at the pre-operative visit, then post-operatively at H6, D1, 1 month, 6 and 12 months and expressed as a percentage variation compared with pre-operative visit results.-c/Post-operative examination of scar appearance by the surgeon at 6 and 12 months using the SCAR (Scar Cosmesis Assessment and Rating) scale.2/- a/VAS of abdominal flexibility in the following areas: hypogastrium, and right and left iliac fossa, at one year assessed by an independent osteopath, scores ranging from 0 to 10 (0 corresponding to normal flexibility and 10 to total rigidity).- b/Consultations in addition to conventional care (medical and non-medical)- c)Use of analgesics and hormonal treatments reported by patients during the first postoperative year-d)Pregnancy achievement during the first postoperative year3/The International Physical Activity Questionnaire (IPAQ) assessed before surgery, at 6 and 12 months after surgery.4/Short-term compliance in terms of number of days and frequency of mobilizations, assessed on a weekly basis for up to 6 weeks,. Long-term compliance is assessed monthly post-cycle in terms of whether and how often mobilizations were performed, and if used in cases of pain.

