**Methods:**

This pilot study is a prospective, randomized, phase II superiority trial. Patients undergoing surgery for infiltrating endometriosis will be randomized, with a 2:1 ratio, into two groups. The intervention group (n = 42) will receive six sessions of osteopathic visceral mobilization with training in abdominal self-mobilization techniques, one preoperative, and five postoperative during the first month post-surgery. The control group (n = 21) will receive no osteopathic visceral mobilizations but will be offered an osteopathic session after one year. The primary endpoint is a minimum increase of 20 points (on a 100-point scale) in the Endometriosis Health Profile-30 (EHP-30) global score, at one year. Secondary endpoints include assessment of gastrointestinal quality of life (GIQLI), sexual function (FSFI), urinary symptoms (ICIQ-FLUTS), pain catastrophizing (PCS), as well as scar examination, pelvic pain, abdominal flexibility, use of medical and non-medical care, analgesic and hormonal treatments, pregnancy rate, physical activity, sedentary lifestyle and patient compliance. Statistical analyses will be based on a one-sided α=0.05 and β=0.15, assuming a standard deviation of 25 points in the EHP-30 global score. A total of 42 participants in the intervention group and 21 in the control group are required.

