### Sample size

The required number of subjects is based on a comparison between the two randomized groups (experimental group *vs*. control) of the percentage variation in EHP-30 questionnaire scores between the pre-operative visit and at 1 year, with a two-sided first-species risk of error of 5%. For ethical reasons, we chose a 2:1 ratio for randomization.

In the literature, Goncalves et al. reported on the evolution of EHP30 scores (before/after) for a control and treatment group receiving an intervention (yoga sessions) [43]. Variations were small in the control group for the 5 main EHP-30 dimensions, and ranged from 20 to 35 points for the treatment group. Pokrzywinski et al [44]. showed the same before/after differences for a control and treatment group (Elagolix molecule), and defined thresholds of between 20 and 35 points for clinically significant differences.

To demonstrate a difference of 20 points associated with a standard deviation of 25, in percentage variation for EHP-30 questionnaire scores between the pre-operative visit and 1 year, with a statistical power greater than 80%, 38 patients are required in the experimental group and 19 in the control group. To allow for patients leaving the protocol and loss to follow-up, 10% more patients are required in each group. Thus, a total of 63 patients will be recruited (42 in the experimental group and 21 in the control group).

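### The primary endpoint is in EHP-30 points in the abstract but a percentage change in Outcomes and Sample size, and power above 80% is not established for percentage change

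*Protocol article*

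**What the plan says.** The protocol article describes the primary endpoint in three places.

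- **Abstract, Methods.** The endpoint is in points: "The primary endpoint is a minimum increase of 20 points (on a 100-point scale) in the Endometriosis Health Profile-30 (EHP-30) global score, at one year". The SD is also in points: "assuming a standard deviation of 25 points in the EHP-30 global score".
- **Outcomes.** The endpoint is relative to baseline: "The primary outcome is the percentage variation in baseline EHP30 questionnaire scores between the pre-operative visit and at 1 year after surgery". The EHP-30 runs from 0 (best) to 100 (worst).
- **Sample size.** The groups are compared on percentage variation, and the planning sentence begins: "To demonstrate a difference of 20 points associated with a standard deviation of 25, in percentage variation for EHP-30 questionnaire scores". The support for the figure 20 comes from two cited studies. For the yoga trial the text says: "Variations were small in the control group for the 5 main EHP-30 dimensions, and ranged from 20 to 35 points for the treatment group". The drug trial is said to have "defined thresholds of between 20 and 35 points for clinically significant differences".

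Statistical methods plans a Student t test or a Wilcoxon test for the main comparison, chosen by the distribution of the data.

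**The concern.** A change in points and a percentage change from baseline are different variables. A fall of 20 points is 50% of a baseline of 40, 40% of a baseline of 50 and 33% of a baseline of 60. The same benefit therefore counts differently according to where the patient started, and a low baseline can produce a very large percentage.

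Two things follow. First, with two definitions in print, the scale of the primary analysis could be settled after results are known. Second, the numbers 20 and 25 are supported in the article only as points. Calling them percentage variation does not supply an SD for percentage change, and the stated power rests on that SD.

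**Working it through.** **1. Reproduce the plan's figure.** Inputs from Sample size: difference 20, SD 25, two-sided 5%, 2:1 allocation, 38 and 19 evaluable patients.

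- Standard error = 25 × √(1/38 + 1/19) = 25 × 0.281 = 7.02.
- 20 / 7.02 = 2.847, and 2.847 − 1.960 = 0.887. Normal-approximation power = Φ(0.887) = 81.3%.
- Noncentral t with 55 degrees of freedom and d = 20/25 = 0.8: power = 79.9%.
- Adding 10% gives 38 × 1.1 = 41.8 and 19 × 1.1 = 20.9, that is 42 + 21 = 63.

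The figure reproduces, although by t test it is about 80% and not above it. The abstract's one-sided 5% and β = 0.15 would need only 34 and 17, so 38 and 19 come from the Sample size inputs.

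**2. Can 20/25 be converted to percentages?** If every patient had the same baseline B, difference and SD would both be multiplied by 100/B. At B = 50 they become 40 and 50, d stays at 0.8 and power is unchanged. Once baselines vary, the division adds spread and skewness. The conversion then needs the baseline mean and SD, which the article does not give.

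**3. Power if the true effect is 20 points but percentage change is tested.** The baseline figures below are assumptions. All results are simulated with 38 and 19 patients at two-sided 5%.

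Model A: baseline mean 50-60, follow-up SD 25, correlation 0.4, scores kept within 0-100. The implied SD of change is √(baseline SD² + 25² − 2 × 0.4 × baseline SD × 25), which is 22.9, 23.5 and 25.0 points for baseline SDs of 10, 15 and 20.

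| Analysis | Baseline SD 10-15 | Baseline SD 20 |
|---|---|---|
| t test, percentage change | about 77-86% | about 55-73% |
| t test, absolute change | about 83-86% | about 76-79% |

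Across these baseline SDs, a Wilcoxon test on percentage change gives about 76-85%, and the baseline-adjusted score in points about 82-87%. At a baseline SD of 20, the t-test result on percentage change also moves with the way near-zero baselines are handled. The higher power at SD 10-15 partly reflects an SD of change below 25.

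Model B: SD of change fixed at 25 and independent of baseline, baseline mean 40-60 and SD 10-20, control improvement 0 or 15 points. The SD of percentage change is about 44-119 percentage points. Power on percentage change is about 50-78% by t test and about 67-77% by Wilcoxon.

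**4. Check on the adjusted analysis.** In Model A, ignoring the limits of the scale, the residual SD after adjustment is 25 × √(1 − 0.4²) = 22.9. Then d = 20/22.9 = 0.87 and power at 38 and 19 is about 86%, in line with the simulation.

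**The case against.** The strongest defence is that Sample size does attach 20/25 to percentage variation, so the plan nominally powers the endpoint that Outcomes defines. If the target were 20 percentage points and the SD of percentage change 25 percentage points, 38 and 19 would be adequate. This defence limits the conclusion to power that is not established; it does not justify the figures. With an SD of 25 points in absolute change and a common baseline, an SD of 25 percentage points would require a baseline of 100, the worst possible score.

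Some stronger readings are tempting, but the article does not support them:

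- *Power is only 13-50%.* These figures arise if the SD is converted to percentages (36-83 for baselines of 70 down to 30) while the difference stays at 20. No section states that pairing. They apply only to a separate reading in which the target is 20 percentage points and the SD of percentage change is 36-83.
- *The trial cannot be read against its 20-point threshold.* EHP-30 scores at baseline, 6 and 12 months are secondary outcome 1a, analysed by mixed models with a group-by-time term. A contrast in points will be available, though not as the primary result.
- *The Wilcoxon fallback costs power.* It is stated in advance, and at a baseline SD of 20 in Model A it protects power relative to the t test.
- *The pelvic pain VAS repeats the error.* It is "expressed as a percentage variation compared with pre-operative visit results", but it is a secondary outcome and nothing in the article contradicts that choice.
- *The silence of Outcomes on which EHP-30 score is primary is a conflict.* The abstract names the global score, so this is brevity.

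A full protocol or analysis plan may give baseline figures. That would not remove the contradiction between the sections of this article.

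**Conclusion.** The concern holds as a contradiction in the primary endpoint. The abstract uses absolute points, Outcomes and Sample size use percentage variation, and the planning inputs are supported only as points. Power above 80% is therefore not established for percentage change.

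The size of any loss cannot be fixed from the article. It ranges from almost none when baselines are similar between patients to a substantial loss by t test when they are widely spread, and it rests on the assumed baseline mean, baseline SD and correlation. The contradiction in scale depends on none of these assumptions. Because it concerns the primary endpoint, it must be corrected.

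**What to change.** Use one definition in the abstract, Outcomes and Sample size: the EHP-30 core (30-item) global score, 0-100, at 12 months after surgery, compared between arms in absolute points with adjustment for the pre-operative score. State the planning assumption as a between-arm difference of 20 points with an SD of 25 points. Give the unadjusted t-test power at 38 and 19 as about 80%. When rewording the abstract, state the direction of benefit as well, since it speaks of an increase on a scale where 100 is worst.

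Percentage change may stay as a descriptive summary. Changing the pelvic pain VAS is optional.

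The cost is an amendment to the endpoint and sample-size wording and to the primary analysis. The scores are already being collected and the total stays at 63. Recruitment began in January 2025, so 12-month data may accrue from early 2026. The amendment should be dated and made before any between-arm outcome data are examined.

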**Fig 2 pone.0323214.g002:**
[figure not shown]
Flow diagram of MOVENDOP trial.

Both groups benefit from 3 post-operative consultations with the surgeon (at 6 weeks, 6 and 12 months after surgery) and an osteopathic consultation 1 year after surgery for endpoint assessment (abdominal flexibility). In addition, the control group receives training in visceral self-mobilization. Data from patients, surgeons and osteopaths is collected at baseline (pre-operative visit), surgery, post-operative consultations (6 weeks, 6 and 12 months after surgery), 5 post-operative osteopathic interventions and at 1 year after surgery (**Fig 1** and **Fig 2**).

A follow-up booklet distributed to patients according to their randomization group, will allow patients in the experimental group to provide data concerning abdominal self-mobilizations performed during the first year following surgery (frequency of performing osteopathic maneuvers and evaluation of pain), and for both groups to provide data on abdominal flexibility at 12 months, medical and non-medical treatment received, and analgesic and painkiller use during this period.

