### Intervention

#### Surgical technique.

Our surgical technique has previously been described [8,39]. Endometriosis staging is performed after surgery based on rAFS scores. Using laparoscopy as an exclusive approach, complete surgical treatment of endometriosis will be performed, which allows accurate disease stage classification. Superficial peritoneal lesions will be treated using bipolar coagulation or peritoneal excision, and endometriomas by cystectomy as described previously [40]. Recto-vaginal nodules will be treated by shaving or by colorectal resection should a shaving procedure be deemed unsatisfactory. This surgical technique has been previously detailed [41]. In cases of endometriosis invading the sigmoid colon or the small bowel, segmental resection will be performed and ureteral involvement treated by ureteroneocystostomy where necessary, as previously described [42]. In the event of bladder lesions invading the mucosa, a partial cystectomy will be performed and closed using single- or double-layer suturing.

Post-operative consultations with the surgeon (at 6 weeks, 6 and & 12 months) will allow assessment of pain, scarring and post-operative complications.

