### Data collection methods

Data will be collected using 2 different tools: REDCap® electronic data capture and the NoEndo platform. An eCRF (electronic Case Report Form) using REDCap® will be used by the surgeon and clinical research associates to collect patient clinical data at each visit, as per the protocol, i.e., demographic and relevant background data, surgical indication, scar examination, pain assessment, postoperative complications, sick leave, hormonal treatment and follow-up data during the 1^st^ year following surgery for each group. This data concerns abdominal self-mobilizations for the experimental group, and abdominal flexibility and extent of medical and non-medical treatment for both groups. Quality-of-life data will be measured using questionnaires specific to endometriosis (EHP-30, GIQLI, FSFI, ICIQ-FLUTS and PCS), which patients will complete via the platform NoEndo. Comparison of the different scores obtained pre-operatively and at 6 and 12 months post-operatively will enable analysis of changes in quality of life.

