### Statistical methods

Statistical analyses will be carried out using R software (R Core Team (2022). R: A language and environment for statistical computing. R Foundation for Statistical Computing, Vienna, Austria. URL https://www.R-project.org/.).

Descriptions are given in number (N) and percentage (%) for qualitative variables, and in mean and standard deviation (SD) or median and interquartile range for quantitative variables, according to their distributions (Gaussian or not). Missing data will be quantified. Normality will be analyzed using the Shapiro-Wilk test and histograms.

Patients will be described and compared between groups at inclusion according to compliance with eligibility criteria, epidemiological characteristics and clinical features. A description of protocol deviations, patients allocated according to these deviations and reasons for drop-out will also be provided.

Initial comparability of the two groups will be assessed on the main patient characteristics and potential factors associated with the primary endpoint. Any difference between the two groups relating to these characteristics will be determined on the basis of clinical and statistical considerations.

Comparisons between groups will be made systematically 1) without adjustment 2) by adjusting for those factors for which distribution may be unbalanced between groups despite randomization, such as contraception, level of disease severity and post-operative complications. All statistical tests will be performed using a two-sided alpha level of 5%. Certain analyses involving secondary endpoints will be mainly exploratory in nature. As discussed by Feise et al. [47] adjustment of alpha risk will not be proposed systematically, but on a case-by-case basis in the light of clinical and statistical considerations.

The main analysis will be carried out on an intention-to-treat basis. An intention-to-treat population refers to all randomized patients except those for whom consent is not obtained or who withdraw their consent concerning use of their data. A per-protocol analysis will be considered of all randomized patients except for those with one or more major deviations defined as: patients ineligibility, uncompliant patients in the experimental group (less than once a day on average over the first post-operative month), or control group patients who perform visceral mobilizations more than 4 times during the year of their own initiative.

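### Post-operative complications are recorded in both arms but are not a listed outcome, so the plan contains no between-arm estimate of complications or adverse events

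*Protocol article*

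**What the plan says.** **Collection.** Under Surgical technique, the surgeon's post-operative consultations at 6 weeks, 6 months and 12 months "will allow assessment of pain, scarring and post-operative complications". Study design and participant timeline (text after Fig 2) confirms that these visits are common to the arms: "Both groups benefit from 3 post-operative consultations with the surgeon". Data collection methods lists among the eCRF contents "scar examination, pain assessment, postoperative complications, sick leave, hormonal treatment and follow-up data".

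**Outcomes.** The Outcomes section introduces its list with "Secondary outcomes are listed below". The items are five questionnaires, pelvic pain, scar appearance, abdominal flexibility, additional consultations, analgesic and hormonal treatment, pregnancy, physical activity and compliance. Neither complications nor adverse events appear there, in the Abstract, or in the secondary objectives at the end of the Introduction.

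**Analysis.** Statistical methods ties its secondary analyses to secondary objectives 1 to 4. Complications appear once, among the factors whose distribution might differ by arm in spite of randomisation and which are to be adjusted for: "such as contraception, level of disease severity and post-operative complications".

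**Context.** The surgery can be extensive. For sigmoid or small-bowel disease "segmental resection will be performed and ureteral involvement treated by ureteroneocystostomy where necessary", and for bladder lesions invading the mucosa "a partial cystectomy will be performed and closed using single- or double-layer suturing". Under Osteopathic interventions, the experimental arm self-mobilises the abdomen and scars three times a day in the first month. Breathing exercises are done more often in week 1 if self-mobilisation is difficult. The osteopath's sessions are at D6, D10, D14, D18 and W6.

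**The concern.** The tested intervention acts mechanically on the operated area in the weeks after surgery that may involve bowel, bladder or ureter. The Discussion itself says that human data on visceral mobilisation are few, mostly non-randomised and small. In a phase II pilot, the rate of complications by arm is one of the main things a reader will want alongside the quality-of-life result.

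The article fixes both halves of the problem. It sets out an outcome list without complications, and it gives complications a different role, as a covariate. They arise after randomisation and could be affected by the intervention. Under the stated plan, an excess in the experimental arm would be handled as an imbalance to adjust away and would not be estimated as a possible effect. Dropping complications from the covariates would cure that handling but would still leave no safety outcome.

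**Working it through.** **1. What is planned for complications**

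| Step | Where in the protocol article | Complications included? |
|---|---|---|
| Assessed at surgeon visits | Surgical technique | Yes |
| Same visits in both arms | Study design and participant timeline | Yes |
| Recorded in eCRF | Data collection methods | Yes |
| Listed as an outcome | Abstract; Introduction; Outcomes | No |
| Compared in an outcome analysis | Statistical methods | No |
| Used as an adjustment factor | Statistical methods | Yes |

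**2. Whether the listed outcomes could stand in.** GIQLI and ICIQ-FLUTS are scored pre-operatively and at 6 and 12 months. Scar appearance is rated at 6 and 12 months. Pelvic pain is taken at H6, D1, 1 month, 6 and 12 months. Analgesic use and extra consultations cover the first year. Any of these could worsen after a complication, but none counts events, and between D1 and 6 months the only scheduled score is pelvic pain at 1 month.

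**3. The plan's sample size.** Inputs from Sample size: difference 20, SD 25, two-sided 5%, power above 80%, ratio 2:1.
- Control n = (1 + 1/2) × (1.960 + 0.842)² × 25²/20² = 1.5 × 7.85 × 1.5625 = 18.4, rounded up to 19; experimental 2 × 19 = 38.
- Adding 10%: 38 × 1.10 = 41.8, giving 42; 19 × 1.10 = 20.9, giving 21; total 63, as stated.

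These numbers were chosen for quality of life. The next steps ask what they allow for complications.

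**4. Precision for complications with 42 versus 21.** The documents give no complication rate, so every rate here is an assumption.
- No events of a given type: one-sided 95% upper limit = 1 − 0.05^(1/n). For n = 42 this is 6.9%; for n = 21 it is 13.3%.
- Assumed 4/42 versus 2/21 (9.5% in each arm): risk difference 0; Wald half-width = 1.96 × √(0.0952 × 0.9048/42 + 0.0952 × 0.9048/21) = 1.96 × 0.0785 = 15.4 points.
- Assumed 10% in each arm: 1.96 × √(0.09/42 + 0.09/21) = 15.7 points.
- Assumed 20% in each arm: 1.96 × √(0.16/42 + 0.16/21) = 21.0 points.

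Wald intervals are rough with so few events and serve here only to show scale.

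**5. Whether a test would be useful.** Exact power of Fisher's test, two-sided 5%, 42 versus 21:

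| Control rate (assumed) | Experimental rate (assumed) | Power |
|---|---|---|
| 5% | 10% | 2% |
| 10% | 20% | 13% |
| 10% | 30% | 39% |
| 20% | 40% | 31% |

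A non-significant result would mean little. Only estimation is worth planning.

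**The case against.** The strongest objection is that this is a condensed journal article. The full protocol and any SAP are not shown, and adverse-event definitions, grading and safety tables by arm are often left to them. The article never says that complications will go unreported. That stands as far as it goes: a reader might infer that no safety reporting exists anywhere, and the article cannot support that. The point here is narrower. The article prints an explicit outcome list without complications, and it states a use for them that treats them as imbalance.

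A reader might also infer that the trial makes no comparison of harm at all. That is too strong. Pelvic pain, scar appearance, GIQLI, ICIQ-FLUTS, analgesic use and extra consultations are outcomes by arm and could move in the harmful direction. They are indirect signals and do not replace event counts.

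It can be argued that judging imbalance requires looking at complications by arm, so a comparison is implied. Some inspection is implied, but only to choose covariates, and it yields no reported estimate. The unadjusted comparison is also kept alongside the adjusted one, so the main quality-of-life test does not depend on this factor.

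Finally, the Discussion sets no go/no-go rule. It says that a larger study would follow from the expected results, not that a positive result launches one automatically. The yield is limited too, as the power figures show. Both objections bear on the size of the point and not on whether it holds.

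**Conclusion.** The point holds for complications and adverse events. They are collected in both arms, are absent from the stated outcomes, and are used only as an adjustment factor, so the plan as printed produces no between-arm estimate of them. It does not follow that the trial is blind to all harm, or that unseen documents contain no adverse-event reporting.

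The missing estimate would be imprecise: about ±15 points if rates near 10% are assumed, about ±21 points at 20%, and an upper limit of 6.9% if none of 42 experimental patients has a given event. All of these assume that 42 and 21 patients are observed. Wide as it is, it would be the trial's only direct between-arm evidence on complications. This is a worthwhile correction to make before analysis. It does not affect the validity of the primary comparison.

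**What to change.** Add one descriptive secondary safety outcome to Outcomes: the number and proportion of patients with at least one post-operative complication recorded at the common surgeon visits, by 6 weeks and by 12 months. Break it down by type and, where the eCRF records it, by severity, re-operation and readmission.

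Add to Statistical methods:
- Report by randomised arm, in randomised patients who had surgery, since a surgical complication cannot occur without surgery. State how many in each arm were not operated.
- Give the risk difference with a 95% interval suited to small counts (exact or score), with no test threshold and no success rule.
- Tabulate separately any events noted only at the osteopath sessions from D6 to W6. Only the experimental arm has these contacts, and mixing them in would favour detection in that arm.
- Stop describing complications as a factor unbalanced by chance, because they occur after randomisation.

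**Cost.** One outcome line, one table and a short analysis paragraph, with no extra visits or patients. The article says only that post-operative complications are recorded. Severity, re-operation, readmission and events seen at osteopath sessions are not stated to be collected, so eCRF fields may have to be added in a trial that has recruited since January 2025, and details for patients already operated may have to be completed retrospectively. Data collection is planned to run to January 2028, so the outcome can still be specified before analysis. The result will be imprecise and should be presented as such.
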